## Abstract

**Introduction::**

Total knee replacement (TKR) is a surgical procedure that is being increasingly performed as a result of population aging and the increased average human life expectancy in South Korea. Consistent with the growing number of TKR procedures, the number of patients seeking acupuncture for relief from adverse effects, effective pain management, and the enhancement of rehabilitative therapy effects and bodily function after TKR has also been increasing. Thus, an objective examination of the evidence regarding the safety and efficacy of acupuncture treatments is essential. The aim of this study is to verify the hypothesis that the concurrent use of acupuncture treatment and usual care after TKR is more effective, safe, and cost-effective for the relief of TKR symptoms than usual care therapy alone.

**Methods/design::**

This is an open-label, parallel, assessor-blinded randomized controlled trial that includes 50 patients with TKR. After screening the patients and receiving informed consent, the patients are divided into two groups (usual care + acupuncture group and usual care group); the patients will then undergo TKR surgery and will be hospitalized for 2 weeks. The patients will receive a total of 8 acupuncture treatments over 2 weeks after surgery and will be followed up at 3, 4, and 12 weeks after the end of the intervention. The primary outcome is assessed using the Korean version of the Western Ontario and McMaster Universities Arthritis Index (K-WOMAC), and the secondary outcome is measured using the Numerical Rating Scale (NRS), Risk of Fall, and Range of Motion (ROM). Moreover, the cost per quality-adjusted life years (QALYs) is adopted as a primary economic outcome for economic evaluation, and the cost per NRS is adopted as a secondary economic outcome.

**Ethics and dissemination::**

This trial has received complete ethical approval from the Ethics Committee of Catholic Kwandong University International St. Mary's Hospital (IS17ENSS0063). We intend to submit the results to a peer-reviewed journal and/or conferences.

**Trial registration::**

ClinicalTrials.gov Identifier: NCT03633097.

## Introduction

1

Total knee replacement (TKR) is a surgical procedure that is being increasingly performed due to population aging and increased life expectancy in South Korea. The number of TKR procedures increased by over 135%, from 45,879 in 2015 to 62,344 in 2019. The medical cost of public health insurance associated with TKRs totaled 37,077,059,000 won (∼32,638,256 US dollars) in 2015 and increased to 55,499,427,000 won (∼48,850,829 US dollars) in 2019.^[1]^ The age distribution of patients undergoing TKR shows that 36.2% of the patients were aged 60 to 69 years, 48.6% were aged 70 to 79 years, and 8.7% were aged ≥80 years,^[2]^ indicating that TKR is primarily performed on elderly patients. A large number of patients undergo TKR due to degenerative knee arthritis. Consistent with the high incidence of TKR in South Korea, the number of patients seeking acupuncture for pain management and enhancement for rehabilitative therapy effects and bodily function not only before but also after TKR has also been increasing.

In the western-medicine-based clinical settings in South Korea, acupuncture treatment after TKR is considered unsafe regardless of the acupuncture points in use because of the risk of infection and reoperation, and the practice is often rejected or prohibited. Furthermore, according to a recent systematic review, including acupuncture in a rehabilitation program is beneficial as an adjunct to opioids for pain management across several types of postsurgical conditions.^[3]^ However, the results of studies investigating the effect of acupuncture after TKR are not in concordance.^[4–7]^ Moreover, no previous study has examined the efficacy, safety, and cost-effectiveness of post-TKR acupuncture rather than focusing solely on its efficacy.

Therefore, it is worth assessing the effectiveness, safety, and cost-effectiveness of acupuncture as an adjunctive therapy in patients following TKR in a pilot study.

## Objective

2

The aim of this study is to verify the hypothesis that the concurrent use of acupuncture treatment and usual care after TKR is more effective, safe, and cost-effective relieving TKR symptoms than usual care therapy alone.

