### Sample size calculation

3.3

In this clinical trial, changes in the K-WOMAC will be analyzed and assessed to examine the effect of acupuncture on pain and functional improvements in patients who underwent TKR.

Due to the lack of information about domestic clinical trials to examine the K-WOMAC as a primary outcome for assessing the effect of acupuncture on the knee joint, we referred to a study in which aromatherapy massage was performed on patients with knee arthritis (married women).^[8]^

The changes in the K-WOMAC after 2 weeks of aromatherapy massage or regular massage in the experimental and control groups were −6.10 ± 4.05 and 0.24 ± 4.16, respectively. The difference in the K-WOMAC between the groups was 6.34. In this study, the difference in the K-WOMAC between the experimental and control groups is assumed to be 3.60. We referred to previous studies for standard deviations. The level of statistical significance is set at 0.05 (α, two-tailed), and power (1−β) is set at 80%.

The minimum sample size needed to test the statistical significance was calculated using ‘G∗Power 3.1.9.2’ and was found to be 22 participants per group. Considering a 10% dropout rate, 25 participants per group or a total of 50 participants will be recruited.

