#### Safety and adverse events monitoring

3.8.3

The safety assessment includes

1.adverse reactions,2.vital signs, and3.clinical laboratory testing.

The subinvestigator will record the details of any adverse reactions and the use of concomitant medications during the clinical trial in the case report form. In case of an adverse reaction, the symptoms and signs of the adverse reaction, duration (start date/end date), severity, result, significance, causal relationship to the drug under clinical investigation, and measures taken for its alleviation will be recorded. The names, dosages, duration of administration, reason for administration, etc, of the concomitant medications will be recorded in detail.

Clinical laboratory tests will be performed at screening, V5, V9, FU2, and FU3. Since this study will evaluate the safety of the usual care and acupuncture combination, it differs from clinical studies that evaluate the safety and pharmacokinetic properties of drugs. Therefore, this study conducts clinical laboratory tests for the following items for the purpose of the standard safety lab test:

1.hematology: hemoglobin, hematocrit, red blood cell count, white blood cell count, and differential count, platelet count;2.serum chemistry: glucose fasting, aspartate aminotransferase (AST), alanine aminotransferase (ALT), blood urea nitrogen (BUN), electrolytes (sodium, potassium, and chloride), serum creatinine (SCr), erythrocyte sedimentation rate (ESR), C-reactive protein (CRP); and3.coagulation: D-dimer, fibrin degradation products (FDP);4.γ-glutamyl transpeptidase (γ-GTP), alkaline phosphatase, creatinine phosphokinase (CPK), uric acid, total bilirubin, total protein, albumin, osteocalcin, carboxy-terminal collagen crosslinks (CTX), urine analysis: pH, protein (albumin), glucose, leukocyte esterase, and blood were performed only at screening.

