##### Safety variables

3.9.3.3

The number of adverse reactions (vital signs, abnormal values in a physical test, acute reactions observed after vaccination, and local or systemic reactions) will be determined for each group, and their incidence and 95% confidence intervals will be presented. The chi-square test will be used for intergroup comparisons of adverse reactions.

Continuous data such as blood or blood chemistry test parameters, physical test parameters, and vital signs will be presented for each group and assessed using descriptive statistics. A paired *t* test will be used for comparisons before and after the treatment, and Student's *t* test will be used for intergroup comparisons. The frequency and percentage will be presented for categorical data such as urine test results, and McNemar's test will be used to determine normal and abnormal conditions for each visit.

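### The objective is to verify that adding acupuncture is safe, but 25 patients per arm with no safety margin cannot verify this for infection or reoperation, and the safety text does not fit the trial

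*Protocol article*

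**What the plan says.** **Aim.** The Abstract and section 2 (Objective) of the Protocol article state a hypothesis to be verified: that acupuncture with usual care is "more effective, safe, and cost-effective relieving TKR symptoms than usual care therapy alone".

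**The safety concern.** Section 1 (Introduction) reports that acupuncture after TKR is "considered unsafe regardless of the acupuncture points in use because of the risk of infection and reoperation". It closes by proposing to assess "acupuncture as an adjunctive therapy in patients following TKR in a pilot study".

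**Size.** Section 3.3 rests on one endpoint: "changes in the K-WOMAC will be analyzed and assessed to examine the effect of acupuncture on pain and functional improvements". It arrives at 22 per group, and 25 after a 10% dropout allowance. No safety rate, margin or power is given.

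**Safety analysis.** Section 3.9.3.3 counts adverse reactions by group, gives incidence with 95% confidence intervals, and compares groups by chi-square. Besides vital signs, its list of what counts reads "abnormal values in a physical test, acute reactions observed after vaccination, and local or systemic reactions". Section 3.9.1 allows chi-square or Fisher's exact test for categorical variables in general.

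**Recording.** Section 3.8.3 records for each adverse reaction its "causal relationship to the drug under clinical investigation". It also schedules white cell count, ESR and CRP at screening, V5, V9, FU2 and FU3. Section 3.8.4 lets the operating surgeon and principal investigator attribute reactions to the TKR. Symptoms that the principal investigator considers unrelated to the intervention are not classed as adverse reactions of the trial.

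**The concern.** Verifying safety and running a pilot are different aims. To verify safety for a given harm, a trial must be able to exclude an excess of that harm beyond some stated amount. The harms named in the Introduction are serious and, presumably, uncommon. The trial has 25 patients per arm, a size chosen for a questionnaire score, and no stated amount to exclude.

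The safety text adds to the problem. One listed item refers to vaccination, and no vaccine is given. The causality field refers to a drug, and the intervention is acupuncture. Infection and reoperation are not named among the safety variables. Read literally, the form does not ask about the intervention under test, and the analysis need not display the events that prompted the question.

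What is at stake is the published safety conclusion. According to the Introduction, acupuncture after TKR is often refused in orthopaedic settings. A statement that safety was verified would bear on that practice, and 25 patients per arm cannot support it.

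**Working it through.** **1. The plan's own figure.** Inputs from section 3.3: difference 3.60, SDs 4.05 and 4.16, two-sided alpha 0.05, power 80%.
- Pooled SD = √[(4.05² + 4.16²)/2] = 4.105, so the standardised difference is 3.60/4.105 = 0.877.
- The noncentral-t calculation for two independent means gives 21.4, so 22 per arm. With SD 4.16 throughout it gives 21.96, again 22.
- Dropout: 22/0.90 = 24.4, so 25 per arm.

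The stated 22 and 25 reproduce. The K-WOMAC sizing is not at fault here.

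**2. What zero events would show (no assumed rate).** The exact two-sided 95% upper limit for 0 of n is 1 − 0.025^(1/n).
- n = 25: 13.7%.
- n = 22: 15.4%.

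For the difference between arms with no events in either, the Newcombe 95% interval is ± z²/(n + z²) with z = 1.96, that is 3.84/28.84 = 13.3 points for n = 25 and 3.84/25.84 = 14.9 points for n = 22.

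**3. What the between-group test could detect (assumed rates).** The documents give no infection or reoperation rate, so the risks below are assumptions. Power is the sum of the probabilities of all pairs of binomial outcomes with p ≤ 0.05, at 25 per arm.

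| Usual care vs acupuncture | Fisher's exact | Uncorrected chi-square |
|---|---|---|
| 2% vs 4% | under 0.1% | 1.1% |
| 2% vs 6% | 0.2% | 3.7% |
| 1% vs 5% | 0.1% | 2.7% |
| 2% vs 10% | 2.3% | 15.3% |
| 1% vs 20% | 34% | 67% |

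With no events among 25 usual-care patients, Fisher's test needs 6 of 25 in the acupuncture arm (p = 0.022; 5 of 25 gives 0.0502). Uncorrected chi-square needs 4 of 25. At a true risk of 3%, the acupuncture arm would show no event with probability 0.97^25 = 47%.

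**4. Scale of a trial that could exclude a set excess.** With equal true risks p, margin m, one-sided 2.5% and 80% power, n per arm = (1.96 + 0.84)² × 2p(1 − p)/m². For a margin of 2 points, which is also an assumption, this gives 389 per arm at p = 1% and 770 at p = 2%. This shows the distance from the stated aim; it is not a proposal.

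**5. The safety text against the trial.** Section 3.4 describes usual care with or without acupuncture, with no vaccine and no investigational drug. The vaccination item in 3.9.3.3 and the drug causality field in 3.8.3 therefore refer to nothing in the trial.

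**The case against.** The case on the other side has several sound parts.

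- **Estimation is already planned.** Section 3.9.3.3 promises incidence with 95% confidence intervals, and section 3.9.1 allows Fisher's test. Both are right. But the intervals will be as wide as shown in step 2, and Fisher's test has less power than uncorrected chi-square. Neither allows verification.
- **Infection is not ignored.** CRP, ESR and white cell count are scheduled. Local or systemic reactions are on the list and could cover infection and needle-site events. Section 3.8.4 makes an infection diagnosed in the recovery room a reason for termination, and section 3.9.3.4.4 mentions surgical site infections. This stands, but none of it commits the plan to reporting infection or reoperation by arm, and section 3.8.4 allows an event attributed to surgery to leave the count.
- **Named events may be left to a fuller document.** That is fair for the omission alone. It does not excuse text that is present and does not fit the trial.
- **The objective may mean only safe, not safer, and it does not itself mention infection.** That is a possible reading. The link comes from the Introduction, and neither reading can be verified at this size.
- **Low power for rare harms is ordinary in 50 patients.** Agreed; it is a fault only because the objective claims more.

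A reader might infer three stronger things. The first is that the reaction list was taken from a vaccine study; the article shows one misfitting item and says nothing of its origin. The second is that a non-significant test would be declared proof of safety; no such decision rule is stated. The third is that only one pooled count will be compared; section 3.9.3.3 does not say so.

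**Conclusion.** The point holds as a mismatch between the stated safety aim and the design, together with two misfitting pieces of safety text. The central result rests on no assumed event rate: zero events in the acupuncture arm would be compatible with a true risk of up to 13.7% (25 patients) or 15.4% (22 patients). Since no safety margin is stated, a non-significant comparison could not establish safety either.

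The power figures depend on the assumed risks. For the assumed risks from 2% vs 4% up to 2% vs 10%, power is at most about 15% by uncorrected chi-square and about 2% by Fisher's test. Only a very large excess, such as 1% vs 20%, would have an appreciable chance of detection.

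The finding does not touch the efficacy sample size or the primary analysis, and it does not call for a larger trial. The pilot label in the Introduction already describes what the design can deliver; the objective should say the same.

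**What to change.** - **Abstract and section 2.** Restate the safety aim as pilot estimation of the incidence of relevant harms by arm. Drop the claim to verify safety.
- **Section 3.9.3.3.** Replace the vaccination item with surgical-site or joint infection, reoperation and needle-site events. Report them by arm to FU3 regardless of attribution, with exact 95% intervals for each rate and an interval for the difference. Use Fisher's exact test where counts are sparse; the reason is a valid p-value, not a gain in power. State that a non-significant comparison is not evidence of safety.
- **Section 3.8.3.** Record the causal relationship to acupuncture in place of the drug.

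**Cost.** Wording in these sections and the matching case report form fields, with no extra patients or visits. The price is a more modest safety claim.

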## Methods

3

### Trial registration

3.1

This study has been registered at ClinicalTrials.gov (trial registration number: NCT03633097; trial protocol version 2.0; https://clinicaltrials.gov/ct2/show/NCT03633097).

### Study design

3.2

This study was designed as an open-label, parallel, assessor-blinded randomized controlled trial. This study will be conducted at Catholic Kwandong University International St. Mary's Hospital in Incheon, South Korea. The clinical trial and the items to be examined are presented in Figure 1 and Table 1. The patients will receive a full explanation of the trial details from investigators. Through this procedure, if they agree to participate in the trial, a signed consent form will be obtained.

**Figure 1 F1:**
[figure not shown]
Study Flow Chart.

**Table 1 T1:** Clinical trial schedule and observation items.

	Study period											Follow-up		
	Screening	W1					W2					W3	W4	W12
Tasks	V1	OP	V2	V3	V4	V5	V6	V7	V8	V9	V10^∗^	F/U1^†^	F/U2	F/U3
Obtaining consent forms from participants	●													
Demographic investigation	●													
History investigation (medical history, previous medication use)	●													
Participant screening	●													
Randomization	●													
Acupuncture + UC			●	●	●	●	●	●	●	●	●^‡^			
UC			●	●	●	●	●	●	●	●	●^‡^			
Efficacy test														
K-WOMAC	●										●		●	
NRS	●		●				●				●	●	●	●
Risk of fall	●										●			●
ROM	●						●				●		●	●
Safety assessment														
Vital signs	●		●	●	●	●	●	●	●	●	●		●	●
Adverse reaction assessment			●	●	●	●	●	●	●	●	●	●	●	●
Laboratory test	●					●				●			●	●
Investigation on the doses of medications that can be administered if needed													●	●
Treatment compliance assessment											●			
Investigation on concomitant medications	●		●	●	●	●	●	●	●	●	●	●	●	●
Investigation on blindness maintenance (examiner)											●			
Cost-effectiveness evaluation	●										●		●	●

<visit schedule: window period included>	Visit 7: 6 days (POD 9 ± 2 day)
Visit 1: 7 days to −1 day from Visit 2	Visit 8: 7 days (POD 10 ± 2 days)
Visit 2: 0 days (POD 3 ± 2 days)	Visit 9: 8 days (POD 11 ± 2 days)
Visit 3: 1 day (POD 4 ± 2 days)	Visit 10: 3 days within Visit 9
Visit 4: 2 days (POD 5 ± 2 days)	FU 1: 3 weeks within Visit 2 (21 days ± 5 days)
Visit 5: 3 days (POD 6 ± 2 days)	FU 2: 4 weeks within Visit 2 (28 days ± 5 days)
Visit 6: 5 days (POD 8 ± 2 days)	FU 3: 12 weeks within Visit 2 (84 days ± 5 days)

OP = operation, POD = postoperative day, UC = usual care.

∗ Previous visit ± 3 days.

† FU1 will be performed through a phone call.

‡ PRN medications needed during the FU period are provided to both groups on the day of discharge.

The patients visited the hospital five times for evaluation. The screening (Visit 1, V1) included only those participants who submitted the informed consent form. For screening, the demographic information, medical history, physical examination, vital signs, questionnaire survey, laboratory test, and selection/exclusion criteria will be evaluated. Randomization and group allocation will be performed at screening. Fifty patients were enrolled and randomly divided into two groups. Patients who have passed the screening test will have a TKR and will be hospitalized in ∼2 weeks with usual care or usual care plus acupuncture therapy.

The patients will receive a total of eight acupuncture treatments over 2 weeks after surgery (four sessions between 3 and 8 days after surgery and four sessions between 9 and 14 days after surgery). They will be followed up at 3, 4, and 12 weeks after the end of the intervention. The primary outcomes will be assessed at V1, V10, and Week 4 of follow-up. The safety evaluations include adverse reaction evaluations, vital sign assessments, and laboratory tests. The adverse reaction evaluation will be performed every day during the hospitalization period and continued during follow-up at 3, 4, and 12 weeks after surgery. The vital sign assessment will also be performed daily during the hospitalization period after surgery and at 4 and 14 weeks of the follow-up. Laboratory tests will be performed during screening, at V5 and V9, and at 4 and 12 weeks of follow-up. An economic evaluation will be performed during the treatment period (2 weeks) and at 4 and 12 weeks after surgery and will investigate medical costs and utility (quality of life) to estimate the quality-adjusted life years (QALYs). The Euro-Qol five dimension scale (EQ-5D), a multiattribute health measurement instrument, will be used to assess the quality of life at baseline (Week 1) and at 2 and 4 weeks. Medical costs will also be investigated at baseline (week 1) and at 2, 4, and 12 weeks for a total of four assessments. These evaluations are performed simultaneously with the clinical trial through in-person interviews during the survey period and through in-person interviews, phone calls, and online communication using questionnaires thereafter according to a predefined arrangement with the patient.

The coordinators of the trial will inform the patient of the next visit schedule for each visit and encourage participation. The clinical trial conductor will instruct the participant to ensure compliance with the treatment.

Only those patients who completed the informed consent form with full acceptance of the expected effects and predicted adverse reactions to clinical trial interventions prior to the commencement of the study may participate in the study. In the event of an accident or adverse event, appropriate measures will be taken according to the investigator's judgment, and the participant will be compensated. Moreover, the study will be conducted ethically in compliance with the principles of the Good Clinical Practice (GCP) guidelines and the revised version of the Declaration of Helsinki.

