###### Economic evaluation parameters and criteria

3.9.3.4.2

The medical costs generated as a result of this clinical trial will be calculated through a medical cost analysis in the economic evaluation. If necessary, the health insurance and medical costs at the present institution may be used to represent a portion of the unit costs. A sensitivity analysis will be performed on the medical costs.

1.Primary economic outcomes(a)Cost per QALY gained(b)The EQ-5D will be used to estimate the quality of life needed to calculate the QALY. Quality of life will be used as the primary economic outcome. The area-under-the-curve method will be used to calculate the QALYs.2.Secondary economic outcome(a)Effectiveness indices such as the cost per NRS3.Economic evaluation period

The initial analysis will take 4 weeks. If further estimation is necessary after 4 weeks, the costs and effectiveness will be extrapolated using a regression model, or secondary analyses such as a decision analysis will be performed.

Medical costs generated as a result of this clinical trial will be calculated based on the number of treatment sessions and unit costs. Researchers will determine and record the medical costs generated inside the clinical trial institution by reviewing the electronic records after they are unblinded.

If the time horizon exceeds 12 months, the unit of cost will be unified to the South Korean won of 2017, and a 5% discount will be applied in accordance with the economic evaluation guideline by the Health Insurance Review and Assessment Service. The analytical point of view of this study is society's point of view. The representative values (e.g., mean, etc) of the parameters used in this study will be used in a baseline analysis. A probabilistic sensitivity analysis will be performed using the distributions of all the estimated parameters and their representative values.

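### EQ-5D is listed only to week 4 although Section 3.2 also places utility at week 12, and a societal perspective is declared while only medical costs are named

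*Protocol article*

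**What the plan says.** **Utility and cost schedule (protocol article, Section 3.2).** The general statement is that "An economic evaluation will be performed during the treatment period (2 weeks) and at 4 and 12 weeks after surgery" and that it "will investigate medical costs and utility (quality of life) to estimate the quality-adjusted life years (QALYs". The next sentence narrows the utility part: the EQ-5D "will be used to assess the quality of life at baseline (Week 1) and at 2 and 4 weeks". Costs run longer: "Medical costs will also be investigated at baseline (week 1) and at 2, 4, and 12 weeks for a total of four assessments".

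**Table 1.** A single row, "Cost-effectiveness evaluation", is marked at V1 (screening), V10, FU2 and FU3. It does not separate costs from EQ-5D.

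**Horizon (Section 3.9.3.4.2).** "The initial analysis will take 4 weeks". For any estimate beyond that, costs and effectiveness are both to be extrapolated by regression, or a decision analysis is to be done. QALYs are computed by area under the curve.

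**Perspective and costs (Section 3.9.3.4.2).** "The analytical point of view of this study is society's point of view". The costs described are medical costs, built from treatment sessions and unit costs. For costs at the trial site: "Researchers will determine and record the medical costs generated inside the clinical trial institution by reviewing the electronic records after they are unblinded".

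**The concern.** Cost per QALY is the primary economic outcome, and cost-effectiveness is one of the three claims in the trial's objective. Three things in the text leave it unsettled.

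- Someone running the week-12 visit cannot tell whether to give the EQ-5D. One sentence of Section 3.2 implies it, and the next leaves it out.
- Costs are measured at week 12, but the 4-week analysis has no use for them. A 12-week analysis would have measured costs and no measured utility. Table 1 does schedule the NRS at FU3, so the secondary economic outcome (cost per NRS) can reach week 12 on measured data while the primary one cannot.
- The perspective label promises more than the costs named. If only medical costs are collected, the result should not be presented as a societal one.

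A smaller point is the baseline label. Section 3.2 ties it to Week 1, which in Table 1 heads the operation and the first post-operative visits. The first economic mark in Table 1 is at screening. For the NRS, Section 3.8.2 lists screening and baseline as separate times, so the word baseline does not settle the matter.

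**Working it through.** The article states no utility, QALY or cost figure, so there is none of the plan's own to reproduce. The check sets the schedules side by side and then shows what the missing time point does to the area under the curve.

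**Step 1: schedules.**

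| Source | Baseline | Week 2 | Week 4 | Week 12 |
|---|---|---|---|---|
| Section 3.2, general statement (costs and utility) | not stated | treatment period | yes | yes |
| Section 3.2, EQ-5D | yes | yes | yes | **not listed** |
| Section 3.2, medical costs | yes | yes | yes | yes |
| Table 1, undivided row | V1 | V10 | FU2 | FU3 |

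The first two rows disagree at week 12. Table 1 cannot settle it, because its FU3 mark is satisfied by costs alone.

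**Step 2: 4-week horizon.** With utilities u0, u2, u4 and the trapezoidal rule,

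QALY(4) = [2 × (u0 + u2)/2 + 2 × (u2 + u4)/2] / 52 = (u0 + 2·u2 + u4) / 52.

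All three utilities are scheduled, and costs are taken at the same times. No extrapolation is needed.

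**Step 3: 12-week horizon.** The added piece is 8 × (u4 + u12)/2 / 52 = 4 × (u4 + u12) / 52. By the EQ-5D sentence, u12 is never measured. The share of the period without utility data is 8/12 = 67%. The carry-forward rule in Section 3.9.3.4.3 is for dropouts and does not cover a visit at which the questionnaire is not scheduled.

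**Step 4: how much the unmeasured weeks matter.** Assumption, since the article gives no utility difference: the arms differ by 0 at baseline and by d at weeks 2 and 4.

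- 4-week gain: (0 + 2d + d)/52 = 3d/52.
- 12-week gain if the difference falls linearly to 0 by week 12: 3d/52 + 4d/52 = 7d/52.
- 12-week gain if the difference stays at d: 3d/52 + 8d/52 = 11d/52.

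| d (assumed) | 4-week gain | 12-week gain, falling to 0 | 12-week gain, held at d |
|---|---|---|---|
| 0.05 | 0.0029 | 0.0067 | 0.0106 |
| 0.10 | 0.0058 | 0.0135 | 0.0212 |

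The two 12-week values differ by a factor of 11/7 = 1.57 whatever d is. For the same cost difference, the 12-week cost per QALY would differ by that factor purely through the extrapolation rule.

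**Step 5: baseline.** In Step 2, u0 carries weight 1 of 4 weeks, or 25% of the 4-week curve, so its date should be explicit. The four marks in Table 1 match the four cost assessments in Section 3.2 one to one, which points to V1.

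**Step 6: perspective.** Each cost named in Sections 3.2 and 3.9.3.4.2 is a medical cost. No patient time, transport, caregiving or productivity cost is named beside the societal label.

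**The case against.** The strongest reply is that the plan is coherent on timing where it matters. Section 3.9.3.4.2 sets the initial analysis at 4 weeks, EQ-5D and cost times agree up to that point, and anything later is to be extrapolated for costs and effectiveness together. This stands. A reader might infer that the cost per QALY cannot be computed, or that 12-week costs will be divided by 4-week QALYs so that the ratio is inflated. The article supports neither: it nowhere describes such a division.

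A reader might also take the FU3 mark in Table 1 as proof that EQ-5D is scheduled there. The row is undivided, so it is not.

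On baseline, the one-to-one match with Table 1 makes V1 the natural reading, so this is loose labelling rather than a missing start point.

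On perspective, Section 3.2 also provides for interviews, phone calls and online questionnaires, and the record review is limited to costs arising inside the institution. That leaves room for patient-reported costs, and a condensed article may omit a list of cost items. It cannot therefore be concluded that non-medical costs will not be collected. What remains is that the text names medical costs only, in both sections, and calls the result societal.

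The reply does not remove the contradiction within Section 3.2, nor does it explain why utility should be extrapolated to a visit that patients attend.

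**Conclusion.** The point holds as an inconsistency to be reconciled and a cheap gain to be had. It does not make the planned 4-week analysis invalid. Section 3.2 contradicts itself on whether utility is measured at week 12. If it is not, a 12-week cost per QALY would rest on extrapolated utility for 8 of 12 weeks. With the assumed utility paths above, the choice of extrapolation alone moves the 12-week QALY gain by a factor of 1.57. That factor depends on the assumed shapes, and the absolute gains depend on the assumed d. The societal label does not match the costs named, and the baseline label needs tightening. None of this touches the K-WOMAC primary outcome.

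**What to change.** - **Section 3.2 and Table 1:** give the EQ-5D at V1, V10, FU2 and FU3, and split the Table 1 row into costs and EQ-5D. A 12-week cost per QALY can then be reported from measured data beside the stated 4-week analysis. The 4-week horizon can stay as the initial analysis.
- **If EQ-5D is not added at FU3:** say that the cost-per-QALY analysis uses costs only up to week 4, and correct the sentence that places utility at week 12.
- **Baseline:** state that it is V1, before surgery. Adjust the QALY difference between arms for baseline EQ-5D, which is already collected.
- **Perspective (Section 3.9.3.4.2):** either relabel it to match the medical costs collected, or add non-medical cost questions to the interviews already planned and keep the societal label.

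The cost is one short questionnaire at an existing visit, plus wording. Keeping the societal label would also add a few questions to the existing interviews.
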